## Abstract

**Background:**

Colorectal cancer is common in North America. Two surgical options exist for rectal cancer patients: low anterior resection with re-establishment of bowel continuity, and abdominoperineal resection with a permanent stoma. A rectal cancer decision aid was developed using the International Patient Decision Aid Standards to facilitate patients being more actively involved in making this decision with the surgeon. The overall aim of this study is to evaluate this decision aid and explore barriers and facilitators to implementing in clinical practice.

**Methods:**

First, a pre- and post- study will be guided by the Ottawa Decision Support Framework. Eligible patients from a colorectal cancer center include: 1) adult patients diagnosed with rectal cancer, 2) tumour at a maximum of 10 cm from anal verge, and 3) surgeon screened candidates eligible to consider both low anterior resection and abdominoperineal resection. Patients will be given a paper-version and online link to the decision aid to review at home. Using validated tools, the primary outcomes will be decisional conflict and knowledge of surgical options. Secondary outcomes will be patient’s preference, values associated with options, readiness for decision-making, acceptability of the decision aid, and feasibility of its implementation in clinical practice. Proposed analysis includes paired t-test, Wilcoxon, and descriptive statistics.

Second, a survey will be conducted to identify the barriers and facilitators of using the decision aid in clinical practice. Eligible participants include Canadian surgeons working with rectal cancer patients. Surgeons will be given a pre-notification, questionnaire, and three reminders. The survey package will include the patient decision aid and a facilitators and barriers survey previously validated among physicians and nurses. Principal component analysis will be performed to determine common themes, and logistic regression will be used to identify variables associated with the intention to use the decision aid.

**Discussion:**

This study will evaluate the impact of the rectal cancer decision aid on patients and help with planning strategies to overcome barriers and facilitate implementation of the decision aid in routine clinical practice. To our knowledge this is the first study designed to evaluate a decision aid in the field of colorectal surgery.

## Background

Colorectal cancer is the third most common cancer accounting for 13% all new cancer diagnoses in Canada [1]. Rectal cancer comprises any tumor in the last 15 cm of the large intestine. The treatment of rectal cancer is especially challenging given the pelvic anatomy and the related muscles and nerves involved in sphincter control, as well as bladder and sexual functions. Two surgical therapies exist for rectal cancer patients: low anterior resection (LAR) with re-establishment of bowel continuity, and abdominoperineal resection (APR) with a permanent stoma. Each procedure presents a particular set of benefits and risks. While LAR is associated with higher risks of leakage at the intestinal re-connection and fecal incontinence; APR is associated with higher risks of stoma related hernia, prolapse, skin damage, and surgery related infections [2]. LAR combined with neoadjuvant therapy has seen a significant rise in surgical practices, especially given the non-inferior oncological outcomes in patient survival when compared to APR [2]. Although it was once believed that avoiding a permanent stoma would improve quality of life, recent literature has questioned the validity of that claim [3-6].

A meta-analysis identified APR as having better global psychological and emotional scores, while LAR was associated with better physical symptom and pain scores. However, results for overall quality of life (QoL), despite being measured by various validated instruments, were consistently equivocal [7]. Similarly, a recently updated Cochrane Review has revealed that low anterior resection (LAR) did not lead to superior QoL [8]. Given the equivalent survival outcomes, and the need to weigh QoL outcomes, the decision for rectal cancer surgery is therefore a value-laden one that deserves the consideration of the patient perspective.

Evidence suggests that patients have played a passive role in the decision process: the decision traditionally relies on three factors including 1) patient’s baseline functional status, 2) surgeon preference, and 3) tumour characteristics [7]. Greater involvement of patients in decision-making may lead to higher quality decisions congruent with patient preferences.

Shared decision making (SDM) is a model that seeks to include both the patients and their healthcare providers in the decision making process [9]. It encourages patients to play an active role in decisions concerning their health, which is a goal of patient-centered care [10]. This model of care has been endorsed by the recent Salzburg Declaration [11] and the US National Academy recommendations on State and Federal SDM implementation [12]. SDM can be facilitated by patient decision aids (PtDA), which are defined as interventions designed to help people make specific and deliberative choices among options by providing information on the options and outcomes relevant to the patient’s health status [13]. The effectiveness of PtDA has been demonstrated in at least three separate systematic reviews [14,15]. They have been shown to improve patient knowledge, lower decisional conflict related to feeling uninformed and unclear about personal values, reduce the proportion of people who were passive in decision making post-intervention, and improve agreement between patient values and health care option chosen [14]. Furthermore, exposure to decision aids can lead to a higher proportion of people with accurate risk perceptions [14]. Despite the demonstrated value of decision aids, a thorough search through the Ottawa Decision Support A to Z Inventory and Decision Aid Library Inventory (DALI) [16], comprehensive catalogues of decision aids, did not return any decision tools to engage rectal cancer patients in the decision-making process regarding the most appropriate surgical treatment for them.

In 2003, consensus standards for PtDAs were established by the International Patient Decision Aid Standards Collaboration (IPDAS) [17]. Through the Delphi method, the IPDAS involved over 100 major stakeholders such as patients, practitioners, researchers and policy makers to develop the criteria for the assessment of the quality of PtDAs. The Ottawa Decision Support Framework (ODSF) is a decision making framework informed by cognitive, social, and organizational psychological theory that guides the assessment and development of PtDAs [18]. This framework contributed to the development of the IPDAS [19]. Guidelines [20] put forth by the ODSF have been used in the development of at least 31 decision aids that were involved in 24 randomized controlled trials [21]. Adhering to quality criteria set by the IPDAS and using the ODSF as a template, a rectal cancer PtDA was developed (Additional file 1) following three principal steps: 1) A systematic review to explore the long term side effects of rectal cancer surgeries; 2) Needs assessments on rectal cancer patients and colorectal surgeons; 3) Development of a decision aid. The systematic review identified that bowel dysfunction after surgical therapies was high [22]. The needs assessments identified a lack of awareness of surgical options and their outcomes, as well as a general lack of patient involvement in the decision making process [23]. The needs assessment also identified that despite the practitioners expressing commitment to shared decision making, their view of the population to which this could apply was limited. The need for a rectal cancer decision aid was identified to encourage quality communication between patients and their practitioners. The decision aid was then designed by integrating evidence-based knowledge on the benefits and risks associated with LAR and APR. Since development, its content and presentation have been reviewed by a patient and a surgeon, but it has not been formally evaluated.

As the rectal cancer decision aid has been developed, the current study is the next step with aims to evaluate and implement the decision aid. The first phase of the proposed study will continue to follow recommendations of the ODSF to evaluate the decision aid with patients at the point of decision making [20] via a pre- and post-DA design.

Adoption of evidence does not solely rely on the evaluation from patients, as decision making is a process that involves both the patients and the healthcare professionals. Patients’ input is necessary but their perception alone has not been sufficient to change clinical practice [24,25]. It is not surprising that even though patient decision aids may foster SDM [26,27], it has been shown that wide spread use in clinical practice has been poor [28-30]. Given the effectiveness of PtDAs, significantly more effort is needed to understand the factors preventing their integration into clinical practice [31]. The Knowledge-to-Action Cycle is a dynamic and reiterative guiding framework to outline strategies for implementation and application of knowledge [32,33]. It is a framework used by the Canadian Institutes of Health Research (CIHR) for transfer of research findings into practice [34]. It promotes the identification of potential barriers as a necessary step prior to developing an implementation strategy for the wide use of an intervention [32].

Furthermore to maintain practice change, there needs to be interventions designed to address the contextual factors that may affect the implementation [35]. A systematic review reported that the three most commonly cited barriers by health professionals are: 1) time pressure; 2) lack of SDM applicability due to patient characteristics; 3) lack of SDM applicability due to the clinical situation [24]. These results indicate that healthcare professionals in general are feeling mounting pressure from limited resources, and that practitioners may be selecting patients for SDM. This knowledge helps inform strategies for future implementation.

To address health professionals’ barriers to use the rectal cancer decision aid, the second phase of the proposed study will explore the issues perceived by the potential adopters—the surgeons working with rectal cancer patients in North America. The assessment of facilitators and barriers specific to the rectal cancer decision aid will help establish the factors associated with the healthcare professionals and the practice environment, and provide direction for selecting and tailoring implementation strategies.

Taken together, decision aids are a platform for shared decision making, an important goal for patient-centred care. Following the guidelines of the Ottawa Decision Support Framework, a rectal cancer surgery PtDA has been developed but not evaluated. In addition, the assessment on patients’ perspective alone is insufficient for the successful implementation of the decision aid in a clinical setting. Evidence translation into clinical practice needs to involve the healthcare professionals. The current study seeks to address these two issues by evaluating the decision aid on patients and exploring the barriers and facilitators of implementation.

### Study objectives

The current thesis study aims to 1) evaluate the effect of a decision aid on patients’ choice and decision-making process and 2) explore surgeons perception of the facilitators and barriers influencing implementation of the rectal cancer decision aid for patients who are considering low anterior resection versus abdominoperineal resection.

## Methods

### Part 1: pre- and post- PtDA study

Research questions:

1) What is the effect of a decision aid on patients’ choices and decision-making processes, among rectal cancer patients?

2) What is the acceptability of the rectal cancer decision aid among patients?

3) What is the feasibility of implementing the decision aid into usual clinical practice?

### Study design

A before and after study will be used to evaluate the decision aid. A review examining PtDA evaluative studies showed that before/after studies and randomized controlled trials have both demonstrated DA effect on choice, patient comfort with decision making, outcomes of decisions, and patient acceptability [36]. In addition, the rectal cancer PtDA was developed according to the ODSF, which has a strong theoretical foundation that has been extensively validated [19]. Given the Ottawa framework has already been evaluated over 20 RCT’s, a pre- and post- DA design was identified as appropriate to explore PtDA effect on decisional conflict before and after intervention, acceptability as perceived by patients, and the feasibility of implementing the DA into usual clinical practice.

### Participants

The study will take place in a tertiary care hospital serving a population of 1.3 million people. The Colorectal Assessment Centre at the Ottawa Hospital receives on average 12 rectal cancer patient referrals per month. Approximately half (6/12) of these patients would be eligible for the study. Eligible participants are 1) patients with newly diagnosed stage I-III rectal cancer confirmed by biopsy; 2) tumor located at a maximum of 10 cm proximal to anal verge; 3) surgeon screened candidates eligible to consider LAR and APR; 4) age ≥ 18; and 5) able to understand and sign informed consent form in English. Patients with existing or previous stoma will be excluded.

### Study intervention

A self-administered rectal cancer surgery decision aid that was developed according to the International Patient Decision Aid Standards (IPDAS) to be used prior to the consultation with the surgeon. During development, a systematic review on long-term postoperative bowel dysfunction and needs assessment were performed and indicated a need for a rectal cancer surgical decision aid. Its content was informed by the highest evidence from existing literature. The decision tool synthesized information on options and their benefits and harms, a values-clarification exercise and guidance in the steps of decision making. The goal of the decision aid is to enhance patients’ knowledge of surgical options, clarify their values associated with each option, and thus foster decisions that are value-congruent. The decision aid is available in paper-based and web-based interactive formats, using both figures and statistics to convey evidence-based knowledge. Patients will receive both versions of the decision aid as part of the intervention and may choose to use one, or both formats. This decision aid will be used as an adjunct to counseling with the health care team.

On the day of return to clinic for surgical consent, a single page summary sheet will be created based on collected patient data for use by the surgeon and patient.

### Procedure

Recruitment will occur at the initial visit at a Cancer Assessment Centre. After completing consent, patients will answer a pre-decision aid questionnaire on paper for baseline measures on knowledge, preferred choice, and decisional conflict while in clinic. Participants are then asked to view the decision aid (paper-based, web-based, or both) in its entirety (Additional file 1) at home, and answer a post-decision aid questionnaire (Additional file 1) (on paper, on the web, or both) that assesses the acceptability of the decision aid, knowledge, value, decisional conflict, preferred choice, and preparation for decision-making. In this study, we will aim to obtain answers from participants within three weeks of their initial visit at the cancer centre by placing a phone call. This process can limit the time lapse between the viewing of the decision aid and answering the post-PtDA questions. Patients who do not view the PtDA or who are difficult to contact within three weeks, will be encouraged to send in the answers in a stamped envelope included in their package.

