### Outcomes

#### Primary outcome measure

The primary outcome will be decisional conflict and knowledge of surgical options. The decisional conflict scale and knowledge test will be used before and after decision aid. The mean scores will be compared using paired t-test. Knowledge test will be a score on 4 questions reflecting key points in knowledge to make decisions.

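### Knowledge, a listed primary outcome, is tested in clinic before the aid is viewed and then at home with the aid to hand, so the gain may partly reflect answers read off the aid

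*Protocol article*

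**What the plan says.** All references are to the protocol article.

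- **Baseline test (Procedure).** After consent, "patients will answer a pre-decision aid questionnaire on paper for baseline measures on knowledge, preferred choice, and decisional conflict while in clinic".
- **Access to the aid (Study intervention).** "Patients will receive both versions of the decision aid as part of the intervention and may choose to use one, or both formats".
- **Post-aid test (Procedure).** Patients view the aid "at home, and answer a post-decision aid questionnaire". The form may be completed "on paper, on the web, or both) that assesses the acceptability of the decision aid, knowledge, value, decisional conflict" and other scales, so knowledge is among the items answered at home.
- **Collection of answers (Procedure).** "we will aim to obtain answers from participants within three weeks of their initial visit at the cancer centre by placing a phone call". Patients who have not viewed the aid, or who are hard to reach in that time, "will be encouraged to send in the answers in a stamped envelope included in their package".
- **Status and score (Primary outcome measure).** "The primary outcome will be decisional conflict and knowledge of surgical options", and "Knowledge test will be a score on 4 questions reflecting key points in knowledge to make decisions". Pre and post means are compared by paired t-test.

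Nowhere does the article say that the aid is put away, that answers are given from memory, or that the post-aid test is supervised. The Discussion names the single arm and the lack of control and blinding as limitations, but not the change in test conditions.

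**The concern.** A pre-post difference measures change only if the instrument is applied under comparable conditions both times. Here the conditions differ in setting, in mode and, most importantly, in access to the answers. At baseline the patient has not seen the aid. At the second test the patient has the paper copy and the web version at home, and the four questions concern the kind of content that the aid supplies.

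Look-up can only raise the second score, so any that occurs pushes the comparison towards a gain. It is a bias and not noise: recruiting more patients does not remove it, and makes a gain of this origin more likely to reach significance. In a single-arm study no comparison group shares the open-book condition, so the effect cannot be subtracted.

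The stated purpose of the aid (Study intervention) is to improve what patients know before they see the surgeon. A score copied from the aid would not show that, and the paired t-test cannot tell the two apart.

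**Working it through.** **1. The plan's own figure.** Sample size gives alpha 0.05, power 0.80, SD 0.6 and a difference of 0.3 in decisional conflict. Taking 0.6 as the SD of the paired differences and a two-sided test, d = 0.3/0.6 = 0.5. The noncentral t distribution gives n = 34 (power 0.808), and 34/(1 − 0.10) = 37.8, rounded up to 38. Both stated figures reproduce. They concern decisional conflict only, and this point leaves them unchanged.

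**2. Test conditions side by side.**

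| | Baseline | Post-aid |
|---|---|---|
| Setting | Clinic | Home |
| Mode | Paper | Paper, web, phone call or mail |
| Aid available to consult | Not yet viewed | Paper and web versions in the patient's possession |
| Closed-book condition | Not needed | None stated |

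**3. Possible size if look-up raises the mean score.** The documents give neither a look-up rate nor an SD for the knowledge change, so these inputs are assumptions: mean lift m of 0.2 to 0.8 of 4 points (5 to 20 percentage points per item), change SD s of 1.0 to 1.4, and no true learning. For n = 34, the noncentrality is (m/s)·√34 with 33 degrees of freedom, and the two-sided critical value is 2.035. For example, m = 0.4 and s = 1.2 give 0.333 × 5.831 = 1.94 and a probability of 0.471.

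Probability of p<0.05:

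| Lift m | s = 1.0 | s = 1.2 | s = 1.4 |
|---|---|---|---|
| 0.2 | 0.205 | 0.157 | 0.128 |
| 0.4 | 0.620 | 0.471 | 0.366 |
| 0.6 | 0.924 | 0.808 | 0.679 |
| 0.8 | 0.995 | 0.965 | 0.899 |

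The range is about 13% to 99%. With 38 pairs, the case m = 0.4, s = 1.2 rises from 0.471 to 0.517, which illustrates that a larger sample does not help.

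**4. A second model as a cross-check.** Suppose a share q of patients looks up all four answers and the rest score as at baseline. Each item is answered correctly without look-up with probability p of 0.4 to 0.6, and the two scores are independent within a patient. The mean spurious gain is 4·q·(1 − p). For q = 0.2 and p = 0.5 it is 4 × 0.2 × 0.5 = 0.40 points. Simulation of 20,000 studies of 34 pairs gave:

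| Share q | Mean spurious gain (of 4) | Studies with a significant gain |
|---|---|---|
| 0% | 0 | about 2.5% |
| 10% | 0.16 to 0.24 | 9% to 14% |
| 20% | 0.32 to 0.48 | 23% to 38% |
| 30% | 0.48 to 0.72 | 45% to 67% |
| 50% | 0.80 to 1.20 | 86% to 97% |

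At q = 0.2 and p = 0.5 the change SD is about 1.56, above the range in step 3, and 31% of studies are significant, against 37% to 62% for the same 0.4-point lift in step 3. Correlated scores would lower that SD. The answer clearly depends on the inputs.

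**The case against.** **The phone call may already limit look-up.** On a plain reading answers are sought by phone, with mail as the fallback, and a caller reading out four questions leaves less room for searching. This stands in part. But the text could also describe a mere prompt, its stated purpose is to shorten the interval between viewing and answering, the aid is still in the home during the call, and the self-completed routes stay open.

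**Additional file 1 is not shown.** It holds the post-aid questionnaire, and an instruction to answer without the aid may be printed there. This cannot be excluded, and if it is there that part of the fix is already done. It would not make the home test supervised.

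**Look-up is inferred.** A reader might conclude that the gain does measure look-up, or that a significant result would be spurious. The documents do not support that: nothing says patients consult the aid while answering, and the Background reports that decision aids have been shown to improve knowledge. What is documented is the unequal access, not its use.

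**The stakes are limited.** The sample size rests on decisional conflict, which Instruments calls the primary outcome. The outcome section does not claim long-term retention, and the Discussion already cautions against causal inference. All true, but the abstract and the outcome section both list knowledge as primary, and this bias, unlike the missing control arm, can be reduced without changing the design.

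**Conclusion.** The point holds as a weakness in how one of two listed primary outcomes is measured. Test conditions differ between the two time points in a way that can only favour a gain, the article states no closed-book condition, and no control arm removes the effect. The knowledge gain may therefore partly reflect answers read off the aid.

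How much is unknown. The 13% to 99% range rests entirely on assumed lifts and SDs and on zero true learning; it shows that the effect could be anything from modest to decisive and is neither an estimate nor a bound. If few patients look up answers, the excess over the nominal 2.5% in the direction of a gain is small in absolute terms (9% to 14% of studies when one in ten does so). The decisional conflict sample size of 34, inflated to 38, stands. The change is worth making because it is cheap and the outcome is primary.

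**What to change.** 1. Ask the four post-aid knowledge items in the phone call already planned within three weeks, from memory and with the patient asked to put the aid away first. The other scales can stay in the home questionnaire.
2. Print the same instruction on the paper and web forms, unless Additional file 1 already carries it.
3. For every patient, record the mode (phone, paper, web, mail) and whether the aid was consulted while answering.
4. Report a sensitivity analysis of the knowledge change that excludes answers given with the aid or by unsupervised routes.
5. Name the difference in test conditions in the limitations.

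The cost is a few extra minutes per call for up to 38 patients and a small amendment to the procedure. Phone answers would be compared with paper baseline answers, a mode difference of unknown size that should be acknowledged. Testing on paper in clinic at the surgical consent visit would match baseline mode, but it would lengthen the interval that Procedure tries to keep short and add a task to a visit whose length is itself a feasibility outcome, so the call is the better place.

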### Sample size

A convenience sample of patients at The Ottawa Hospital who have rectal cancer and meet the eligibility criteria will be invited to participate. A paired t-test will be used to compare the means of ‘decisional conflict’ score measured before and after the PtDA implementation. Assuming a significance level of 0.05, power of 0.80, an expected standard deviation of 0.6 [38], our required sample size is 34 to detect a clinically relevant difference of 0.3 in the decisional conflict score. The minimal clinical difference for the DCS scale was previously established because this difference is able to discriminate people who make decisions from those who delay decisions in a validation study by O’Connor [37]. Accounting for a drop out rate of 10%, our estimated sample size is 38. The study will continue until the recruitment target of 38 patients has been reached.

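### Post-aid questionnaires may be mailed in without the aid having been viewed and with no closing date, so the before/after comparison may include unexposed patients and late, post-counselling answers

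*Protocol article*

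**What the plan says.** All references are to the protocol article.

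- **Procedure.** Patients complete the baseline questionnaire in clinic, look at the aid at home, and then answer the post-aid questionnaire. Staff telephone with the aim of having answers within three weeks of the initial visit. The section says this keeps the gap between viewing and answering short. It then adds: "Patients who do not view the PtDA or who are difficult to contact within three weeks, will be encouraged to send in the answers", using a stamped envelope. No last date for mailed answers is given.
- **Primary outcome measure.** "The decisional conflict scale and knowledge test will be used before and after decision aid", and the mean scores are compared by paired t-test.
- **Study intervention.** The aid is "to be used prior to the consultation with the surgeon" and is an adjunct to counselling by the care team. A one-page summary drawn from the patient's collected data is prepared on the day of return for surgical consent.
- **Sample size.** "our required sample size is 34 to detect a clinically relevant difference of 0.3 in the decisional conflict score"; and "Accounting for a drop out rate of 10%, our estimated sample size is 38".

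**The concern.** With no control arm, the change is tied to the aid only by what happens between the two measurements. The Procedure section leaves that interval open in two ways.

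First, read plainly, it solicits post-aid answers from people who have not viewed the aid. For them there is no measurement after the aid, so including them pulls the mean change towards zero. The same form carries the acceptability and preparation-for-decision-making scales, which someone who has not seen the aid cannot meaningfully complete.

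Second, three weeks is an aim, counted from the clinic visit and not from viewing, and the mail route has no limit. A mailed form could therefore be completed after the return visit for surgical consent. Any fall in decisional conflict or gain in knowledge produced by the surgeon's counselling would then be credited to the aid.

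The Discussion concedes that a single uncontrolled arm weakens causal inference, but does not address exposure or form timing. Those are the parts that can be put right cheaply.

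**Working it through.** **Inputs from the Sample size section.** "Assuming a significance level of 0.05, power of 0.80, an expected standard deviation of 0.6"; difference 0.3; 34 pairs; 10% dropout. Sidedness is not stated, and neither is whether 0.6 is the standard deviation (SD) of the paired difference. Both are settled by what reproduces the plan's number.

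**Reproducing the plan.** For a paired t-test with SD of the difference 0.6 and two-sided 0.05, the noncentrality is (0.3/0.6)·√n.
- n = 34: noncentrality 0.5 × √34 = 2.915, power 0.808.
- n = 33: power 0.795. The smallest sufficient n is therefore 34, as stated.
- 34/0.9 = 37.8, rounded up to 38, as stated.

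The sample size arithmetic is not in error. A one-sided test would need 27 and does not match.

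**Dilution by non-viewers.** Assume a share f of the 34 pairs are non-viewers with no change on average, and viewers change by 0.3.
- Mean change: 0.3(1 − f).
- Variance: 0.36 + 0.09·f(1 − f).

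| f (assumed) | mean change | SD | power at 34 pairs |
|---|---|---|---|
| 0 | 0.30 | 0.600 | 0.81 |
| 10% | 0.27 | 0.607 | 0.71 |
| 20% | 0.24 | 0.612 | 0.60 |
| 30% | 0.21 | 0.616 | 0.49 |

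Holding the SD at 0.6 gives 0.72, 0.62 and 0.51 in the last three rows, so the variance assumption matters little.

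**Contamination by late forms.** Assume the aid has no effect, a share q of forms is completed after counselling, and counselling alone shifts the score by c.
- Mean change: q·c.
- Variance: 0.36 + c²·q(1 − q).

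The entries are the probability of p < 0.05 at 34 pairs.

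| q (assumed) | c = 0.15 | c = 0.3 |
|---|---|---|
| 10% | 5% | 6% |
| 30% | 7% | 13% |
| 50% | 11% | 28% |

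The documents give no value for f, q or c. All of these figures concern decisional conflict. The article gives no effect size or SD for the four-question knowledge test, so no equivalent calculation is possible there.

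**Cost of restricting the comparison.** With the full effect of 0.3 in the pairs that remain, losing 30% of 34 leaves 24 (34 × 0.7 = 23.8) and power 0.65. Losing 50% leaves 17 and power 0.49. If the 30% are non-viewers with no change, dropping them (0.65) costs less power than keeping them (0.49). If they are late forms from patients who did view the aid, dropping them is a real loss of power.

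**The case against.** - **The sentence is ambiguous.** The three-week phrase may govern both clauses, so that it describes patients who have not yet viewed the aid when telephoned and who later view it and mail the form. The acceptability and preparation scales on that form fit this reading. This stands: a reader might infer that people who never see the aid are certainly counted, and the text does not settle that. The missing closing date remains on either reading.
- **Collecting answers is not analysing them.** Nothing says that non-viewers' or late answers enter the paired t-test, and an analysis plan not shown may define the analysis set. This stands in part. Such a plan could not separate these forms unless viewing status and completion dates are collected.
- **Counselling within the interval is possible, not stated.** The aid is meant to be used before the consultation, and the consent-day summary implies that answers are expected by then. This stands. No stated rule enforces it for mailed forms, and the timing of the return visit is not given.
- **Baseline timing.** A reader might infer that baseline is taken before the surgeon has spoken to the patient, so that counselling falls inside the interval for everyone. The article does not say so. Participants are "surgeon screened candidates eligible to consider LAR and APR", and baseline follows consent, so the screening itself would naturally come first. Assuming a counselling shift of 0.3 in every patient merely returns the design's own power under another name.
- **Restriction selects compliant patients.** Making viewers with timely forms the only analysis set is a per-protocol choice, and its cost grows with the share removed. This stands, and is why an all-enrolled analysis belongs beside it.

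**Conclusion.** The point holds as a risk created by the stated procedure, not as a demonstrated bias. The Procedure section invites post-aid forms without requiring prior viewing, without a closing date and without requiring completion before the consent visit. The before/after contrast may therefore contain unexposed patients and, among late mailings, the effect of counselling.

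With an assumed 10% or 20% of non-viewers who do not change, power at 34 pairs drops from 0.81 to about 0.71 or 0.60. Contamination is negligible when 10% of forms are late (5–6% false positives). It becomes material only at larger shares: 7–13% at 30% and 11–28% at 50%, for an assumed counselling shift of 0.15 to 0.3. The two mechanisms act in opposite directions and the shares are unknown, so the net direction cannot be determined. The documents do not support a claim that every patient's change is contaminated, or that the stated sample size is wrong. The matter should be put right because the remedy is cheap and the missing dates could not reliably be reconstructed afterwards.

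**What to change.** No visit or element of care needs to move.

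1. Reword the Procedure sentence so that the post-aid form is to be completed after the aid has been viewed and before the return visit for surgical consent, and make clear whether it refers to patients who have not viewed the aid at all or only not yet.
2. Record on the form whether the aid was viewed, the date of viewing and the date of completion.
3. In the paired tests of decisional conflict and knowledge, count as post-aid only forms dated after viewing and before the consent visit.
4. Report non-viewers and late forms separately, and leave non-viewers out of the acceptability and preparation scores.
5. Give an all-enrolled analysis alongside, because restricting to viewers with timely forms selects compliant patients.

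The cost is two dates, one yes/no item and some procedure wording. Some pairs will also leave the main comparison. The plan allows for 10% dropout only, so power suffers if late or unviewed forms are common (0.65 at 24 pairs, 0.49 at 17). Telephone reminders that prompt viewing and completion before the consent visit would keep that number down.
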